### **Participant timeline**

This pilot study will be conducted between December 2020 and November 2021. Participating centers and participants will be recruited in December 2020. Both hospitals and patients will go through their eligibility screening respectively. Eligible hospitals and patients will then be informed about the study, potential benefits and risks, and be asked for consent. Consented hospitals will be randomized into intervention or control arm before the commencement of the study. Eligible patients will be assessed through collecting their baseline demographics, disease history, and clinical characteristics during hospitalization. On the day of discharge, eligible patients in intervention hospitals will receive influenza vaccine shots. Face-to-face follow-up visits for each patient will be scheduled at 1-month and 3-month post discharge. Study outcome data will be collected during the follow-up visits. If the patient is unable to return for such a visit, they will receive a telephone call instead.

### **Sample size**

As this is a pilot trial and the primary objective is to test the feasibility of increasing influenza vaccination uptake in HF patients, other than to test the efficacy or effectiveness of intervention, a practical number of 11 participating sites and inpatients

with HF during one month (30 patients on average) from each site are set. Intra-cluster correlation coefficient of 3-month death or rehospitalization due to heart failure will be calculated using the outcome of each individual from each cluster.

### **Recruitment**

An estimated average of 30 patients per hospital will be set for recruitment. The admission list from each participating site will be monitored to ensure recruiting consecutive heart failure patients to prevent potential selection bias. If a quota of 50 patients is reached in any given hospital, the recruitment process will end.

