| Rationale              | 
Considerable data support the broad benefits of influenza vaccination in the general population. However, there is uncertainty over the effectiveness of influenza vaccination in preventing cardiovascular events in the high-risk population such as those with HF. Influenza vaccination is not covered by medical insurance in majority of China. The rate of influenza vaccination was as low as 0.6% in Chinese patients with HF, compared to about 60% in the Western European countries and in the US. Thus, it is of critical importance to detect whether providing free influenza vaccine, providing vaccination service in hospital, and educating patients as well as health provider will increase vaccine rate among patients hospitalized due to severe symptoms of HF. If so, whether improved influenza vaccine rates in patients with HF will reduced all-cause death or HF hospitalization. Before a definitive randomized cluster randomized trial, a pilot study is planned to address the following uncertainties for the design of future definitive study:
 
 
(i) Whether the intervention package is feasible;
 
(ii) Whether a target influenza vaccine rate of 90% is achievable in the intervention clusters;
 
(iii) Proportion of patients hospitalized with HF getting influenza vaccination in routine care;
 
(iv) Number of patients will be enrolled in future study.
 
 |

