| Number of participants | 330 patients; recruitment from 11 hospitals in one influenza season (average of 30 patients per hospital).                                                                                                                                                                                                                                                                                                                                                                                                                                                                                                                                                                                                                                                                                                                                                                                                                                                                                                                                                                                                                                                                                                                                                                                                                                                                                                                                                                           |

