### **Trial design**

This pilot trial is a two-arm, parallel, hospital-based, cluster randomized trial where 7 hospitals will be randomized to intervention and 4 hospitals to control arm. All eligible HF inpatients from each hospital will be recruited during 2020 November. Intervention includes (i) education of the health care team and patients; (ii) provision of free vaccine on the day of discharge; and (iii) provision of immunization service inside hospital before discharge.

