### **Outcomes**

#### *Primary outcome*

- Rate of uptake of influenza vaccination among eligible patients in the intervention hospitals and that in the control hospitals;
- Number of patient recruited;
- Rate of adherence to follow-up;

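### The 50-patient stop per hospital conflicts with recruiting every eligible inpatient in the month and right-censors the recruitment count wherever it is reached

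*Protocol*

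**What the plan says.** Three places in the protocol define a site's sample by a time window:

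- Trial design: "All eligible HF inpatients from each hospital will be recruited during 2020 November".
- Patients: the first inclusion criterion takes in all adults discharged with a heart failure (HF) diagnosis in the recruitment month, subject to NYHA class III-IV and consent.
- Sample size: inpatients "with HF during one month (30 patients on average) from each site are set".

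The Recruitment section gives the same expected size, "An estimated average of 30 patients per hospital will be set for recruitment", and then adds a second stopping rule: "If a quota of 50 patients is reached in any given hospital, the recruitment process will end".

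The count that this rule limits is an outcome. The Methods list "Number of patient recruited" as primary, while the Synopsis lists it as secondary. The Synopsis and Background both name "Number of patients will be enrolled in future study" as something the pilot must settle. The statistical considerations in the Synopsis and the Analysis section both report recruitment as a number. Figure 1 lists a recruitment rate as an assessment, but no denominator is defined for it anywhere.

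**The concern.** A hospital with a 51st eligible, consenting patient in the month cannot follow both rules, and nothing in the text says which prevails.

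The second issue is what the count then means. If one hospital enrols 50 patients in 15 days and another takes 30 days, both report 50. Their rates are 50/15 = 3.3 and 50/30 = 1.7 patients per day, or 100 and 50 per 30 days. The raw count hides a twofold difference.

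The hospitals affected are the largest ones, which say most about upper recruitment capacity and about variation in cluster size. Both quantities are inputs to planning a cluster trial.

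**Working it through.** **The plan's own figure.** The Synopsis gives "330 patients; recruitment from 11 hospitals in one influenza season (average of 30 patients per hospital"). 11 x 30 = 330, which reproduces. With the cap, the trial cannot exceed 11 x 50 = 550, and the cap is 50/30 = 1.67 times the planned average.

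**Inputs from the protocol.** 11 hospitals, a mean of 30 recruited per hospital, and a cap of 50. Sites need capacity for more than 35 HF patients per month, with no ceiling stated. That figure counts all HF patients treated, not only those in NYHA III-IV who consent, so it does not show that the cap will bind.

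**Assumption.** The protocol gives no between-hospital spread. Let X be a hospital's monthly number of eligible, consenting patients. Take X as Poisson, or as gamma-Poisson (negative binomial) with the hospital means having a CV of 0.3, 0.5 or 0.7.

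**Formulas.** The uncapped SD is sqrt(mean + (CV x mean)^2). At CV 0.5 this is sqrt(30 + 15^2) = 16.0. The capped mean and SD are those of min(X, 50). The chance that at least one hospital exceeds 50 is 1 - (1 - P(X > 50))^11. At CV 0.5 this is 1 - (1 - 0.107)^11 = 71%.

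**Results at the protocol's mean of 30:**

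| Assumed CV | P(X > 50) | P(any of 11 > 50) | Capped mean | Understatement | SD, uncapped to capped |
|---|---|---|---|---|---|
| 0 (Poisson) | 0.03% | 0.3% | 30.0 | 0.0% | 5.5 to 5.5 |
| 0.3 | 4.0% | 36% | 29.7 | 0.9% | 10.5 to 9.9 |
| 0.5 | 10.7% | 71% | 28.7 | 4.4% | 16.0 to 13.0 |
| 0.7 | 15.5% | 84% | 27.0 | 10.0% | 21.7 to 15.3 |

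If the true mean were 40 (an assumption, not the protocol's figure), CV 0.5 would give a mean of 35.3 and an SD of 13.2 in place of 21.0.

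**Does this carry through to the definitive trial's size?** For mean cluster size m, cluster-size CV c and intra-cluster correlation (ICC) rho, the number of hospitals needed is proportional to rho(1 + c^2) + (1 - rho)/m. A smaller m raises it and a smaller c lowers it. The protocol plans to estimate an ICC but gives no value, so 0.01 to 0.05 is assumed. At mean 30 and CV 0.5, c^2 is (16.0/30)^2 = 0.28 uncapped and (13.0/28.7)^2 = 0.21 capped.

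- rho = 0.01: 0.0458 uncapped, 0.0466 capped, a change of +1.7%.
- rho = 0.02: 0.0583 for both, a change of 0%.
- rho = 0.05: 0.0958 uncapped, 0.0935 capped, a change of -2.5%.

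Over the same ICC range the change is +0.4% to -0.4% at CV 0.3 and +3.4% to -6.1% at CV 0.7. With a mean of 40 and CV 0.5 it is +5.2% to -4.1%.

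**The case against.** A per-hospital cap is an ordinary feasibility choice. It stops one site dominating an 11-cluster pilot, and the protocol calls its sample size a practical number. The quota can be read as an unstated exception to the all-eligible rule. At the stated mean, with little spread between hospitals, it would almost never bind. Much of the information is also recoverable. The admission list is monitored, there are screening and discharge forms, and dated enrolment would normally show when the 50th patient was reached. How to express the recruitment rate named in Figure 1 could be left to an analysis plan.

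Most of this stands, and it is why the point is minor. It does not remove the conflict between the two rules. Nor does the protocol promise to keep counting eligible patients once a hospital has stopped, and that count is hard to rebuild later.

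Three stronger readings are tempting, and the documents do not support them:

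- *The definitive trial would be mis-sized.* The calculation above shows a small net effect whose sign depends on an ICC that the protocol does not give.
- *One hospital reaching 50 ends recruitment everywhere.* The quota sentence refers to any given hospital and plainly means that hospital.
- *The cap introduces selection bias.* The first 50 consecutive patients are not a selected subset of their own time window. What is lost is the rest of the window.

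**Conclusion.** The concern holds as a minor point. The contradiction is in the text and needs no assumption: the sample is set both as everyone eligible in a month and as at most 50 per hospital. The censoring follows wherever a hospital reaches 50.

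Its size cannot be fixed from the protocol. At a mean of 30 the understatement of mean recruitment runs from about 0% to 10% over assumed CVs of 0 to 0.7. The spread is affected more than the mean: at CV 0.5 the SD falls by 18% and the mean by 4%. These figures rest on the gamma-Poisson model and on the protocol's own estimate of 30 being right. They describe how well the pilot would measure recruitment. They do not show that the later trial would have the wrong number of hospitals.

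**What to change.** 1. Keep the cap if it is wanted. State it as an exception in Trial design, in the patient inclusion criteria and in Sample size, so that all three agree with Recruitment.
2. Record the date on which a hospital reaches 50.
3. Continue counting eligible patients on the monitored admission list to the end of the recruitment month. Consent is an inclusion criterion and would not be sought after the cap, so define this count by the other criteria and keep it on the same definition before and after the cap.
4. Report recruitment per hospital as patients per recruiting day (and per 30 days), with the month's eligible count and its SD across hospitals, and flag the capped hospitals.

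The cost is a little more list counting at hospitals that reach the cap, including reading the discharge diagnosis and NYHA class for each patient counted, and one changed summary measure. No extra enrolment is needed.

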### **Data collection methods**

Case report forms (CRFs) at screening, baseline, admission, intervention, vaccination, discharge, 1-month and 3-month follow-up will be designed to collect patient characteristics and study outcomes. Data will be assessed by site investigator team and sampled by steering committee. Outcome data will also be collected for patients who drop out of or drop in to the intervention.

### **Data Management**

An electronic data capture (EDC) system with automatic range checks will be used for data entry and storage. Double entry will be applied to assure data quality.

### **Randomization**

#### *Sequence generation*

In this pilot cluster randomized trial, randomization will be applied to participating sites. Computer-generated random numbers for 11 hospitals with 7 in the intervention arm and 4 in the control arm. Site investigators will enroll participants. All eligible patients in intervention hospitals will receive influenza vaccines.

#### *Blinding*

This is an open label study.

#### *Analysis*

Descriptive analysis will include VCR, number of recruitment, ILI rate and 3-month death or HF readmission in intervention and control hospitals. Clustering effect will be considered when using individual-level data. The proportion of each outcome measure and its confidence interval will be calculated. Analysis will be done at the end of recruitment and the end of follow-up. All statistical analyses will be undertaken using R 3.6.1 (R Foundation for Statistical Computing, Vienna, Austria, <https://www.R-project.org/>). Schedule of PANDA II pilot is in **Figure 1**.

### **Data monitoring**

We plan to use a combination of central (remote) and site monitoring of the accumulating data. Prior to the initiation of the study at any participating center, all designated research staff will be trained on the study procedures by the operational staff. Data collected by research nurse/coordinator should be monitored and verified every day by operational staff. Mistakes found need to be corrected in time. An

independent Data Safety Monitoring Board (DSMB) will meet every month to review the data quality.

### **Harms**

Every patient in this trial will be insured by a contracted insurer. Adverse Event Following Immunization (AEFI) will be reported to steering committee and the manufacturer pharmacovigilance team. AEFI include vaccine product-related reaction, vaccine quality defect-related reaction, immunization error-related reaction, immunization anxiety-related reaction, and coincidental event. Trial insurer and/or vaccine manufacturer will compensate to those who suffer harm from severe AEFI.

### **Audit**

DSMB will audit the trial conduct during the meeting every six month.

### **Protocol amendment**

We plan to communicate important protocol modifications (e.g. changes to eligibility criteria, outcomes, analyses) to relevant parties (e.g. Investigators, ERC/IRBs, trial participants, trial registries, journals, regulators) on investigators meeting every other week.

### **Consent**

In this pilot cluster randomized trial, we plan to obtain the informed consent from each participating site and each individual participant. Informed consent can only be signed if the patient or designated proxy is fully aware of the risks and possible outcomes.

### **Confidentiality**

Personal information about potential and enrolled participants will be collected, shared and maintained by trial staff in order to protect confidentiality before, during and after the trial. The whole process of data collecting and analyzing will be conducted anonymously.

### **Declaration of interest**

This study will be supported by Sanofi Pasteur.

### **Access to data**

The principal investigator will have full access to study data. A data analytical plan is required if intending to apply for data access.

### **Dissemination policy**

The final conclusion of this pilot trial will be released to public through academic conferences, journals or mass media. The release decision will be made by the study steering committee.

### **Funding**

This study will be supported by Sanofi Pasteur (study code: FLU00144).

## Registration

PANDA II pilot will be registered on the [Chinese Clinical Trial Registry](#).

## Ethical and regulatory approval

Ethical and necessary regulatory applications will be sent to corresponding institutional review board and/or regulatory authority.

| TIMEPOINT                                                                 | November                                  | December   | January         | February | March | April     |
| ENROLMENT:                                                         |                                           |            |                 |          |       |           |
| Hospital and patients eligibility screen                                  | X                                         |            |                 |          |       |           |
| Hospital and patients informed consent                                    | X                                         |            |                 |          |       |           |
| Allocation                                                                |                                           | X          |                 |          |       |           |
| INTERVENTIONS:                                                     |                                           |            |                 |          |       |           |
| [Intervention arm (education + vaccination)]                       |                                           | X          |                 |          |       |           |
| [Control arm (usual care)]                                         |                                           | X          |                 |          |       |           |
| ASSESSMENTS:                                                       |                                           |            |                 |          |       |           |
| [baseline demographics, clinical characteristics, and vaccination] | X                                         | X          |                 |          |       |           |
| [recruitment rate]                                                 | X                                         | X          |                 |          |       |           |
| [vaccination logistics, immunization service license]              |                                           |            | X               | X        |       |           |
| [adherence rate]                                                   |                                           |            |                 | X        | X     |           |
| [influenza-like illness, mortality, readmission]                   |                                           | X          | X               | X        | X     | X         |
